###### Secondary Outcomes

Medical records will be used to assess prescription of medication and mortality rate compared with previous existing record, and they will also be used to compare the number of hospitalizations between the control and intervention groups.

ICF scores will be collected using the WHO Disability Assessment Schedule 2.0 (WHODAS 2.0) [33]. The WHODAS 2.0 is a tool for measuring functioning and disability in accordance with the ICF framework. The tool assesses 6 domains of functioning: cognition, mobility, self-care, getting along with others, life activities, and participation in community activities. This study will use the 36-item version that can either be self-administered or administered by a proxy or interviewer.

The Functional Reach Test (FRT) [34] will be used to assess any improvement in physical function and balance.

The FRT is a widely used tool to screen for balance problems in older adults. The test comprises a brief physical task that asks the individual to reach forward without moving his or her feet. The test measures the amount of maximum excursion that the individual is able to cover without losing balance or taking a step.

###### Exploratory Outcomes

####### Physiological Data

The Empatica E4 [20] will be used to measure physiological responses to the SENSE-GARDEN stimuli. These physiological responses will include heart rate and EDA.

####### A Reduction in Depressive Symptoms and Feelings of Loneliness

The Cornell Scale for Depression in Dementia (CSDD) [35] will be used to determine any reduction in depressive symptoms and feelings of loneliness in PWDs. The CSDD is a measure of depression among people with moderate to severe dementia, making it an appropriate choice for the SENSE-GARDEN study. The 19-item tool assesses mood-related signs of depression, behavioral disturbance, physical signs, cyclic functions, and ideational disturbance. It is administered in the form of a semistructured interview by a health care professional or clinician.

####### An Improvement in Quality of Life

The Quality of Life in Late Stage Dementia (QUALID) scale [36] is the only scale developed for advanced dementia and will, therefore, be used to determine any improvement in quality of life in this study. It was created to appreciate the outcome of clinical management, including the effect of therapeutic interventions. QUALID contains 11 items that describe observable behaviors, such as emotional state, interaction with others, aggression, and physical signs of discomfort. It is completed by a health care professional or a family caregiver.

####### Relief From Feelings Related to the Care Burden

A semistructured dyadic interview will be conducted with the PWD and their family caregiver at the end of the study period. This interview will be used to explore the relationship between the 2 individuals. One factor will be the relief from feelings related to the care burden.

###### Informal (Family) Caregiver

####### A Reduction in Caregiver Burden

The Zarit Burden Interview [37] will be used to measure caregiver burden. The tool is a self-report measure that evaluates a caregiver’s health, psychological well-being, finances, social life, and relationship shared with the PWD. Scores range from 0 to 88, with a higher score indicating a higher level of burden.

####### An Improvement in Caregiver Coping and Relief From Stress

The Brief-COPE [38] is a shortened version of the Coping Orientation to Problems Experienced (COPE) inventory [39] and will be used to determine any improvement in the coping strategies in family caregivers. The Brief-COPE is a self-reported measure comprising 28 items that assess the following coping strategies in caregivers: emotion-focused strategies, problem-focused strategies, and dysfunctional coping strategies.

####### An Increased Quality of Visits to the Person With Dementia

The Family Visit Scale for Dementia [40] will be used to evaluate the quality of visits from the family members to the participants with dementia. The questionnaire is completed by the family member and evaluates nursing staff interaction with residents and visitors, meaningfulness of the visit, cleanliness, and connection established between the visitor and the resident.

####### An Improvement in the Quality of the Relationship With the Person With Dementia

The Quality of Carer Patient Relationship scale [41] will be used to assess an improvement in the relationship between the PWD and the family caregiver. This scale comprises 14 items that assess the level of warmth in the relationship and the absence of criticism.

###### Formal (Professional) Caregiver

####### A Reduction in Caregiver Burnout

The Maslach Burnout Inventory–Human Services Survey (MBI-HSS) [42] will be used to assess caregiver burnout in professional caregivers. The MBI-HSS is an extensively used tool for measuring burnout in professionals working in human services. The tool focuses on emotional exhaustion, depersonalization, and personal accomplishment.

### Data Analysis

Quantitative data will be analyzed using SPSS Statistics version 25 (IMB Corp). Stratification by gender, age, and type and stage of dementia will be used to analyze the data. Repeated measures analysis of variance (ANOVA) will be used to assess whether the SENSE-GARDEN intervention has an effect on participants over time. Given the novelty of the SENSE-GARDEN intervention, it is not possible to assess the previous literature for clinically meaningful differences. However, Cohen *d* has been used to determine effect size in studies focusing on the effects of nonpharmacological interventions on behavioral outcomes in PWDs [43].

Cohen *d* is a measure of standardized difference between 2 means [44]. It uses standard deviation units to express the magnitude of difference between the 2 means, indicating the importance of the difference. Cohen has defined a small effect size as *d*=0.2, a medium effect size as *d*=0.5, and a large effect size as *d*=0.8.

For this study, repeated measures ANOVA will be performed on the data using SPSS to assess the effects of the intervention over the numerous time points (T0-T3). We estimate that a sample size of 55 will have over 80% power to detect a medium difference between means at a .05 significance level.

Qualitative interview data will be analyzed using thematic analysis [45]. Thematic analysis is a method of identifying patterns of prevalent ideas or responses and can offer rich insight into the attitudes and beliefs of participants. This aspect of the study will be vital for understanding the users’ experiences of the SENSE-GARDEN.

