### Study Design

For the full trials, a controlled before-after study design will be used. The timeline for the study is shown in Figure 3. All participants eligible for the study will receive the SENSE-GARDEN intervention for 3 months. For the final month of the study, half of the participants (the intervention group) will continue to receive the SENSE-GARDEN intervention. The other half of the participants (the control group) will discontinue visits to the SENSE-GARDEN, receiving only normal care. The randomization procedure will use sealed envelopes and will be performed by the local researcher at each test site. The total number of envelopes will be prepared before the recruitment period. A sealed envelope will be assigned to each participant at the time of her or his enrolment. This randomization is to determine whether visits to the SENSE-GARDEN have lasting effects.

The study will start in August 2019, with a recruiting period of 6 months. The intervention period for each participant will be 3 months, followed by 1 month in either the intervention or control condition. The total study period will be 10 months.

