### Participants

This study will recruit a total of 55 PWDs living in care facilities, in a multisite trial with 3 sites. Details for each site are as follows: (1) Belgium—1 study site, 25 PWDs, 25 informal caregivers, and 3 professional caregivers, (2) Norway—1 study site, 15 PWDs, 15 informal caregivers, and 3 professional caregivers, and (3) Portugal—1 study site, 15 PWDs, 15 informal caregivers, and 3 professional caregivers.

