### Limitations

A limitation of this study proposal is its small sample size. However, although the study may not be able to produce generalizable results, it will provide important insights into the use of a novel technology, such as SENSE-GARDEN for PWDs. The results will provide foundation for further study in the use of immersive, individualized environments and how these environments can be used to facilitate communication and person-centered care in residential care home environments.

A further limitation is the potential variance between the test sites. Implementing this study protocol in 3 different countries may be difficult in terms of ensuring that the SENSE-GARDEN intervention is delivered in the same manner in each care home. Cultural differences between the test sites may mean that methods of facilitation from care home staff could affect the overall SENSE-GARDEN experience, therefore, influencing the results from the study. However, all professional care staff will be given the same training on how to use the SENSE-GARDEN. This training should help to ensure that the intervention is conducted in a similar way at each test site.

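### The planned T0–T3 repeated-measures ANOVA gives no matching test of the randomised question, which only the between-arm comparison at T3 can answer

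*Protocol article*

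**What the plan says.** Study Design (protocol article) gives everyone the intervention for three months. In the final month "half of the participants (the intervention group) will continue to receive the SENSE-GARDEN intervention", while the rest return to usual care. The stated reason for randomising is to learn whether any benefit persists. Envelopes are assigned at enrolment and handled by a local researcher at each site. Outcome Measures places the assessments at baseline (T0), week 4 (T1), week 12 (T2) and week 16 (T3).

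Data Analysis names one quantitative model: "repeated measures ANOVA will be performed on the data using SPSS to assess the effects of the intervention over the numerous time points (T0-T3". The section describes its purpose as finding an effect on participants over time. It does not mention an arm factor, a group-by-time term or a contrast at T3. On factors it says "Stratification by gender, age, and type and stage of dementia will be used to analyze the data". Site is not in that list, although Limitations says "A further limitation is the potential variance between the test sites" and Participants plans 25, 15 and 15 people at the three sites.

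The power statement is that "a sample size of 55 will have over 80% power to detect a medium difference between means at a .05 significance level", with medium defined by "a medium effect size as *d*=0.5". For hospital admissions, Secondary Outcomes says of the medical records that "they will also be used to compare the number of hospitalizations between the control and intervention groups", without giving the period to be compared.

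**The concern.** Randomisation can show an effect only where treatment differs, and it differs only between T2 and T3. A time effect over T0–T3 makes no comparison between arms. Its T3 mean also mixes continuers and stoppers, so a change that includes T3 is not the effect of the intervention in either group. Followed as written, the plan randomises people and then states no test that uses the randomisation.

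Two things are at stake. The term that is finally tested (main effect, interaction or T3 contrast) could be chosen after the data are seen. And an uncontrolled time effect could be reported as if it were the result of a randomised comparison.

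**Working it through.** **Inputs from the article.** N = 55 (Participants); two halves, taken as 27 and 28 (Study Design); d = 0.5 and alpha .05 (Data Analysis), taken as two-sided; visits at weeks 0, 4, 12 and 16 (Outcome Measures).

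**Assumptions, not in the article.** The true arm difference is 0.5 SD at T3 and zero at T0–T2. SDs are equal, nobody drops out, and the correlation between visits is r.

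**1. The article's own figure.**
- Within-person change, 55 people, standardised change 0.5: noncentrality 0.5 × √55 = 3.71 on 54 df, power 0.95.
- Generic repeated-measures input f = 0.25 with four visits: 0.88 or more for the time or group-by-time term, for r from 0 to 0.8.
- Unadjusted difference between arms: 27 × 28 / 55 = 13.75, noncentrality 0.5 × √13.75 = 1.85 on 53 df, power 0.44.

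So the stated power of over 80% reproduces for change over time, and for a generic ANOVA effect size. It does not reproduce for a 0.5 SD difference between the randomised arms.

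**2. Time effect as written.** If continuers and stoppers differ by δ at T3, the pooled T3 mean lies about δ/2 from each group's mean. It describes neither group, and no arm comparison is made.

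**3. Group main effect, if an arm factor is implied.** Averaging (0, 0, 0, 0.5) gives 0.125 SD. The variance of a four-visit mean is (1 + 3r)/4. So λ = 13.75 × 0.125² / [(1 + 3r)/4], on F(1, 53).

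**4. Group-by-time test.** The squared deviations of the arm difference from its mean sum to 3 × 0.125² + 0.375² = 0.1875. So λ = 13.75 × 0.1875 / (1 − r), on F(3, 159).

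**5. T3 adjusted for T2.** The standardised difference becomes 0.5 / √(1 − r²), multiplied by √13.75, on 52 df.

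| r (equal at all visits) | Main effect: λ, power | Group-by-time: λ, power | T3 given T2: difference, power |
|---|---|---|---|
| 0.3 | 0.45, 0.10 | 3.68, 0.32 | 0.52, 0.48 |
| 0.5 | 0.34, 0.09 | 5.15, 0.44 | 0.58, 0.56 |
| 0.7 | 0.28, 0.08 | 8.59, 0.68 | 0.70, 0.72 |
| 0.8 | 0.25, 0.08 | 12.89, 0.86 | 0.83, 0.86 |

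**6. Correlation decaying with time.** These are simulations of 4,000 trials. With correlation 0.7 per 4 weeks, group-by-time has about 40% power uncorrected and 33% with Greenhouse–Geisser, against 72% for T3 given T2. With 0.7 between consecutive visits regardless of spacing, the figures are 44% (Greenhouse–Geisser) against 73%.

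**7. Adjusting for T0 instead of T2.** Under equal correlations nothing is lost. With 0.7 per 4 weeks, the T0–T3 correlation is 0.7⁴ = 0.24 and the standardised difference is 0.5 / √(1 − 0.24²) = 0.515. Power is then about 46%, little above the unadjusted 44%.

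**8. Site.** The article gives no between-site variance, so the gain from adjusting for site cannot be computed.

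**The case against.** The strongest reply is that this is a condensed article. Between-subject factors, contrasts and covariates are usually set out in an analysis plan, and nothing here excludes an arm factor. That stands as far as missing detail goes. But the article does fix the model, its time window, its purpose and a list of factors, and that specification does not fit the design in Study Design.

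Second, the primary objective is a before-after one, and the ANOVA serves it. This also stands. A reader might infer that the planned model answers no question at all. The article does not support that: T0, T1 and T2 are measured under uniform treatment, and contrasts among them address the before-after aim. Only effects that include T3 are mixed.

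Third, the loss of power depends on the term and on the correlation. That is right. The 8–10% belongs to a main effect that the article never proposes, and under equal correlations of about 0.8 or more the group-by-time test loses nothing against T3 given T2.

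Four further inferences are tempting but not supported:
- That the stratification splits 55 people into 16 or more cells. The text does not say that the factors are crossed; one-at-a-time breakdowns fit it equally well.
- That admissions will be counted over all 16 weeks, diluting any difference. Table 1 lists medical records at each of T0–T3, and nothing says that the intervals are pooled. The period is simply not fixed.
- That allocation is stratified by site. The article says only that a local researcher carries it out at each site.
- That the power statement is wrong. It does not name the difference it refers to, and it reproduces for change over time.

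**Conclusion.** The point holds in limited form. The only quantitative model the article names is directed at change over T0–T3, while the arms differ only between T2 and T3. As written, the randomised question has no matching test, and any effect that includes T3 pools two treatment states.

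If an arm factor is implied, the cost for a 0.5 SD difference at T3 ranges from severe (main effect, about 8–10% power) through moderate (group-by-time under equal correlations of 0.3–0.7, about 32–68% against 48–72%) to none (equal correlations of about 0.8 or more). It is larger again if correlation decays. These figures rest on assumed correlations, 27 against 28 people and no dropout.

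A targeted T3 analysis does not by itself secure 80% power for d = 0.5 between arms. In the table it exceeds 80% only at r = 0.8. The case for it is that it answers the question for which people were randomised.

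**What to change.** In Data Analysis, for scale outcomes of the person with dementia and the paired informal caregiver measured at T0–T3:

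- Define the randomised analysis as the between-arm difference at T3 with a 95% CI, adjusted for the T2 score and site (three levels), by ANCOVA or the equivalent T3 contrast in a mixed model.
- State whether allocation stays concealed until week 12. Envelopes are assigned at enrolment, so T2 is measured after randomisation. If concealment to week 12 cannot be assured, adjust for T0, or use a mixed-model T3 contrast that leaves the arm means free at T1 and T2.
- Report T0–T2 change in all participants separately and label it an uncontrolled before-after analysis.
- Base the between-arm comparison of hospitalisations on weeks 12–16.
- Leave professional-caregiver burnout out of the between-arm analysis, because staff are not randomised. Keep non-score outcomes such as mortality and medication out of the ANCOVA.

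The cost is a few sentences, one degree of freedom for the T2 score and two for site. No new visits, data or software are needed.

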### Ethical Approval and Considerations

Applications for ethical approval have been submitted by the 3 study sites in accordance to the national regulation. This study has been submitted to Norway’s Regional Committee for Medical and Health Research Ethics and is currently under assessment (document ID 1094463).

#### Confidentiality and Privacy

Confidentiality of private health information will be ensured according to the regulation (EU) 2016/679 (General Data Protection Regulation). All private personal data will be deidentified: every unique identifying number, characteristic, or code identifier of the individual, relatives, or employers will be removed, so that the information can be used alone or in combination with other information. The resulting data will be analyzed by a statistician to ensure that no individually identifiable health information remains.

#### Informed Consent

The consent of participants will be required. They will be provided a letter of informed consent to be signed, together with an information sheet. The participants will be informed regarding the study’s aims and protocol and what involvement the study will comprise. The participants will be made aware of their right to withdraw from the study at any time. Information regarding confidentiality and data protection will be given. The letter of consent will be signed by the patient, when competent, or otherwise a legal tutor, signing as proxy.

#### Exit Strategy

An important ethical consideration for users is the exit strategy at the end of the project. All care organizations in the consortium have initially expressed their interest in evaluating the potential of keeping the SENSE-GARDEN after project end. The YOUSE GmbH method will be used also in connection with the exit strategy.

## Results

The trials commenced recruitment in August 2019. All data are expected to be collected by the end of May 2020. All phases of the user-centered design process have taken place, which has helped shape the development of SENSE-GARDEN. The results of the first phase have been published and presented at the Fourth International Conference on Human and Social Analytics 2018 (in press). Interviews with 52 users comprising people with mild cognitive impairment and informal and formal caregivers were conducted in November 2017. The aims of these interviews were to collect initial responses and attitudes toward the SENSE-GARDEN concept and investigate what benefits, if any, the users thought SENSE-GARDEN could provide in the care of PWDs.

The interviews were analyzed using thematic analysis [45]. A total of 6 themes were identified: benefits for all, shared experiences, past and present, focus on the individual, emotional stimulation, and challenges to consider. The ideas expressed by the users provided rich insights into how the SENSE-GARDEN intervention should be implemented. For example, a point raised by the users was the importance of caregiver facilitation. Although it is important for the SENSE-GARDEN system to work correctly, it will be essential to involve a caregiver who is able to facilitate the session in a safe and effective way. From this feedback, we are working on creating user training materials that will help the caregivers use the system and also aid them in creating meaningful experiences for the PWD.

**Figure 4 figure4:**
[figure not shown]
Photo of a test session using a prototype of SENSE-GARDEN.

## Discussion

### Summary

This paper has outlined the objectives, study design, and preliminary results of an AAL-funded study, SENSE-GARDEN. To our knowledge, SENSE-GARDEN is the first intervention to combine multisensory stimuli, virtual technology, and autobiographical material to create an immersive and personalized room for PWDs. Our progress thus far has indicated the value of involving user groups in the initial stages of intervention development and has shown that these users have a positive outlook toward SENSE-GARDEN. The evaluation summary report has been provided in Multimedia Appendix 1.

### Limitations

A limitation of this study proposal is its small sample size. However, although the study may not be able to produce generalizable results, it will provide important insights into the use of a novel technology, such as SENSE-GARDEN for PWDs. The results will provide foundation for further study in the use of immersive, individualized environments and how these environments can be used to facilitate communication and person-centered care in residential care home environments.

A further limitation is the potential variance between the test sites. Implementing this study protocol in 3 different countries may be difficult in terms of ensuring that the SENSE-GARDEN intervention is delivered in the same manner in each care home. Cultural differences between the test sites may mean that methods of facilitation from care home staff could affect the overall SENSE-GARDEN experience, therefore, influencing the results from the study. However, all professional care staff will be given the same training on how to use the SENSE-GARDEN. This training should help to ensure that the intervention is conducted in a similar way at each test site.

### Conclusions

Despite these limitations, this study has the potential to provide important contributions to current research on dementia care. The interdisciplinary nature of this project will allow us to evaluate the SENSE-GARDEN from multiple perspectives, such as technical, sociological, and psychological. The findings from the full trials have the potential to offer numerous implications on future research in dementia care and also in promoting person-centered care in practice.

